### **1.5.2 SPECIFIC OBJECTIVE**

The specific objectives of this study are:

1. To describe the baseline sociodemographic, socioeconomic, working experience, training attendance, and means KAP score of food handlers.
2. To develop and implement a theory-based intervention module for food handlers in Selangor, Malaysia.
3. To evaluate the effectiveness of the SCT constructs as the main framework of the intervention module in improving KAP among food handlers between the intervention and control group.

4. To describe and compare the effectiveness of the TRIM-OSH on the change of knowledge, attitude and practice compared to standard training among food handlers between and within groups at the end, and one-month post training, after controlling for covariates.

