## 1.6 RESEARCH HYPOTHESIS

The research hypothesis of this study is:

- H1:** The sociodemographic, socioeconomic, working experience, and training attendance characteristics of the intervention and control groups would be the same.
- H01:** There is no significant differences in the sociodemographic, socioeconomic, working experience, and training attendance characteristics of the intervention and control groups.
- H2:** The KAP on occupational safety and health at food premises of the intervention and control groups at the baseline would be the same.
- H02:** There is no significant differences in the KAP on occupational safety and health at food premises of the intervention and control groups at the baseline.
- H3:** The SCT constructs as the main framework of the intervention module is effective in improving KAP among food handlers between the intervention and control group.
- H03:** The SCT constructs as the main framework of the intervention module have no significant effect in KAP among food handlers between the intervention and control group.
- H4:** The TRIM-OSH effectively improves KAP on occupational safety and health at food premises among food handlers.

**H04:** There is no significant differences in the KAP on occupational safety and health at food premises of the intervention and control groups at post-intervention.

## CHAPTER 2

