### **3.2 Study design**

The study is a randomized controlled trial study. A single blinded, cluster randomized controlled trial study design will be conducted with pre-assessment and post-assessment on the intervention module. The respondents will be divided into two groups, intervention or control. The control group will receive a standard treatment and brochures related to occupational safety and health, while the intervention group will receive a theory-based intervention module on occupational safety and health among food handlers. The duration of the study is within 3-6 months.

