**INTERVENTION MODULE OUTLINE**

**FIRST SESSION (1 HOUR)**

**MAIN OBJECTIVE:**

1. To enhance self efficacy among food handlers on occupational safety and health at food premise

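### Objective 3 and H3 credit the SCT framework, but the two-arm comparison can only test the TRIM-OSH package, so H3 cannot be separated from H4

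*Combined protocol and SAP*

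**What the plan says.** Objective 3 in section 1.5.2 is "To evaluate the effectiveness of the SCT constructs as the main framework of the intervention module in improving KAP among food handlers", comparing the two groups. In section 1.6, H3 states: "The SCT constructs as the main framework of the intervention module is effective in improving KAP among food handlers", judged across the two arms. Its null, H03, is that the constructs "have no significant effect in KAP among food handlers between the intervention and control group". The null for H4 is: "There is no significant differences in the KAP on occupational safety and health at food premises of the intervention and control groups at post-intervention".

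On the arms, section 3.2 (Study design) says that "the intervention group will receive a theory-based intervention module on occupational safety and health among food handlers". Of the comparator, the same section says: "The control group will receive a standard treatment and brochures related to occupational safety and health". The Executive Summary describes the control condition as standard training and does not mention brochures. Section 1.2 describes the compulsory Ministry of Health course as covering food hygiene, food safety and food poisoning, and says that no OSH module is compulsory for food handlers. Section 2.3 adds that such food-safety modules do carry some OSH elements, taught as hygiene, with hand washing as the example. The length of the standard training is not given.

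The Intervention Module Outline in the appendix sets out three sessions of one hour each. Their main objectives are self-efficacy, a supportive working environment and behavioural capability.

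Section 3.10 plans a further analysis of how the SCT components (behaviour, individual, environment) affect KAP. In Chapter 4, Tables B to E compare construct scores between and within arms. Table F is a fixed-effects model with self-efficacy as the outcome and group, time and education as predictors.

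**The concern.** H3 and H4 make different causal claims. H4 says the module works. H3 says the theory on which the module was built makes it work. Both are to be judged between the same two randomised arms. Those arms differ in OSH content and dedicated OSH time as well as in the SCT framework, so randomisation protects the claim about the whole package and nothing finer.

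The distinction has practical consequences. Section 1.3 hopes the results will help the government add an OSH component to the current food handler training, and the Executive Summary aims at national implementation. Whether plain OSH content would be enough, or whether an SCT-based design is needed, bears on that decision. Following H3 as written would allow a conclusion on this question that the trial cannot support.

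**Working it through.** **1. The two hypotheses side by side**

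| | Outcome | Comparison | Claim |
|---|---|---|---|
| H3/H03 | KAP | intervention v control | SCT constructs are effective |
| H4/H04 | KAP | intervention v control | TRIM-OSH is effective |

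Outcome and comparison are the same. Only the claim differs.

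**2. What the comparison estimates**

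Write C for the effect of OSH content and time beyond what control receives, and S for the extra effect of the SCT framework. In additive form, the between-arm KAP difference estimates C + S. H4 concerns C + S; H3 concerns S. One contrast cannot give both.

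The module outline offers no way to separate them. Each session has a construct as its main objective and OSH teaching as its content:
- Session 1: self-efficacy, taught through hazards, risk assessment and risk control.
- Session 2: supportive environment, taught through roles, responsibilities and the importance of training.
- Session 3: behavioural capability, taught through lifting, sharp objects and machines.

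Dedicated OSH time is 3 × 1 = 3 hours with TRIM-OSH. For control, no dedicated OSH session is described.

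**3. How often the KAP contrast is significant when S = 0**

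The plan's own sample size comes first. Section 3.6 starts from 20 clusters of six and allows 20% attrition at each of three follow-ups: 6 / 0.8³ = 11.72, rounded up to 12, and 20 × 12 = 240. This reproduces the stated N. The starting figure of six cannot be checked, because no effect size, SD, ICC or power is given. The Executive Summary gives 139 participants, so both totals are used.

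Assumptions: 20 clusters in total, 1:1 allocation (section 3.5), two-sided alpha of 0.05 (section 3.10 does not state sidedness), S = 0, and C = d standard deviations.

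- Cluster size m = N/20; design effect = 1 + (m − 1) × ICC.
- Effective n per arm = (N/2) / design effect.
- Power = Φ(d × √(n/2) − 1.96).

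Example with N = 240, d = 0.5, ICC = 0.10: m = 12, design effect = 1 + 11 × 0.10 = 2.1, n = 120/2.1 = 57.1. Then 0.5 × √28.6 − 1.96 = 0.71, and Φ(0.71) = 76%.

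Probability that the contrast is significant, from ICC 0.10 to ICC 0:

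| Assumed d | N = 139 | N = 240 |
|---|---|---|
| 0.3 | 29% to 42% | 36% to 64% |
| 0.5 | 65% to 84% | 76% to 97% |
| 0.8 | 96% to over 99% | 99% to over 99% |

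**4. Whether the construct analysis separates C from S**

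Section 3.10 gives no mediation model, does not say whether arm is included, and sets no rule for deciding H3. In Tables B to F the constructs are outcomes; none of these tables relates a construct to KAP.

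Whether arm is included matters. A simulation (2,000 runs, individual level, no clustering) raised KAP and a construct score by the same d in the intervention arm, with no path from construct to KAP and independent errors. Share of runs in which the construct was a significant predictor of KAP:

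| d | N = 139, arm omitted | N = 139, arm included | N = 240, arm omitted | N = 240, arm included |
|---|---|---|---|---|
| 0.3 | 7% | 5% | 6% | 4% |
| 0.5 | 10% | 6% | 14% | 4% |
| 0.8 | 37% | 5% | 59% | 6% |

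With arm included, the rate stays near 5%. Independent errors are a favourable assumption: a shared cause such as motivation or prior training could still link construct and KAP within an arm, because construct levels are not randomised. Even a true construct-KAP path would not show that the SCT framework beats plain OSH teaching, since plain teaching may raise the same scores.

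**The case against.** The strongest reply is that H3 refers to the constructs as the framework of the module and so can be read as meaning the SCT-based package. The claims anticipated in the Executive Summary and the general objective concern TRIM-OSH or the training programme; none says that SCT itself caused the gain. Standard training is also a sensible comparator for that general objective. All of this stands, and the comparator is not at fault. On that reading, however, H3 repeats H4 and still needs rewording.

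Three stronger inferences are tempting, and the documents do not support them.

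- *Any KAP gain would be accepted as proof of SCT.* No such rule is written. Section 3.10 plans a separate construct analysis and lists the effectiveness of the constructs apart from the primary and secondary outcomes. A KAP gain alone need not settle H3. The difficulty is that the plan does not say what would.
- *Control receives no OSH material.* It receives brochures, and section 2.3 finds OSH elements in food-safety modules. What can be said is that no OSH training matched for content and time is described.
- *The construct analysis is worthless because the same sessions raise both scores.* With arm in the model, that mechanism alone does not inflate false positives. Confounding remains, which is a reason to call the analysis exploratory, not to drop it.

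**Conclusion.** The point holds as one of attribution. The design can test whether TRIM-OSH improves KAP against the control condition. It cannot test whether the SCT framework is responsible, and the construct analysis as written does not change that.

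If OSH teaching works and SCT adds nothing, a significant KAP contrast would occur in about 29% of trials (N = 139, 0.3 SD, ICC 0.10) to over 99% (0.8 SD, ICC 0, either N). The effect sizes, the ICCs and the total of 20 clusters are assumptions. The range matters for H3 only if H03 is judged on the plain KAP contrast, which the plan does not specify.

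A reader might take these figures as an inflated type I error. They are not: the test would be correctly rejecting a false null of no package effect, and the error would lie in reading the rejection as evidence for SCT. H4 and the KAP outcomes are unaffected.

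**What to change.** Reword Objective 3 and H3/H03 as the effect of the TRIM-OSH package, versus the control condition, on self-efficacy, behavioural capacity and supportive working environment. This matches Tables B to F.

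In section 3.10, state that any analysis linking construct scores to KAP is exploratory and non-randomised, is fitted with arm in the model, and will not be used to claim that the SCT framework itself caused the KAP gain.

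The reworded objective depends on construct scores being collected. Section 3.7 lists four questionnaire parts, none named for the constructs, so it should say which items produce these scores.

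The cost is wording in three places. No extra arm or larger sample is needed. The downside is a less ambitious claim about theory.

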### LITERATURE REVIEW

#### 2.1 TYPES OF OCCUPATIONAL HAZARDS ENCOUNTERED BY FOOD HANDLERS

Occupational hazards can be present in any workplace. However, depending on the type of food premises they are working, food handlers may be exposed to various hazards that could be detrimental to their safety. To describe the characteristics, hazards at food premises can be classified into physical, chemical, biological, mechanical, and social hazards (Petricciani, 2009).

##### 2.1.1 Physical Hazard

Physical hazards can be defined as factors within the environment that can harm the body with or without direct contact. For example, a food handler involved in processing raw materials such as chicken, seafood, and meat may be exposed to physical hazards due to low temperatures. They might have to work for a long hour in a refrigerated room to prevent the product from spoiling. However, this will expose the workers to more prone to frostbite, respiratory disorders, and rheumatic disorders (Thetkathuek et al., 2015). In contrast, a food handler might work under high temperatures, mainly when allocated near a cooking range. Without a proper ventilation system, the heat produced during the cooking process might cause excessive sweat production, leading to acute dehydration, heat exhaustion, heat cramps, heatstroke, and burns (Zulkarnain et al., 2020).

Another example of physical hazards commonly found at food premises is noise. This is especially common in the food processing industry that involves the use of machines in their processing line, for example, for mixing and grinding purposes, in a factory setting. However, the food handlers who work in the kitchen in hotels,

restaurants, and franchise food chains can also be exposed to the hazard of noise that may come from an exhaust fan, food processor, blender, grinder, etc. Prolonged exposure to excessive noise may lead to non-auditory effects such as anxiety, lethargy, reduced productivity, and increased agitation, besides the much-avoided auditory effects of hearing loss (Mirza et al., 2018). Furthermore, mixing and grinding in the food industry, such as grinding and mixing grain, beans, nuts, and herbs, can also lead to the suspension of dust in the air. This will expose the food handlers to inhalation of dust particles, especially likely to result in respiratory disorders such as Baker's lung disease and allergies (De Matteis et al., 2017).

In the food processing, distribution, or food service segment of the food and beverages industry, food handlers commonly have to perform their work by standing for long hours. In addition, there are also involved in transferring food items that carry a substantial amount of weight at times. Without proper posture and technique, especially during lifting up and putting down a heavy load, can cause recurrent musculoskeletal symptoms such as upper and lower back pain, back and thigh muscle sprain and strain, and prolapsed intervertebral disc in a more severe condition (Bovenzi et al., 2017). In other situations, the working area might have been designed without consideration of the ergonomics of the food handlers. For example, an excessive discrepancy in the height of a working table and the sitting chair of the food handlers may easily cause back discomfort and fatigue.

### **2.1.2 Chemical Hazard**

A chemical hazard can be defined as any chemical preparation in the workplace in any form (solid, liquid, or gas). Besides being involved in the preparation, cooking, and serving of food, food handlers also involve cleaning the customers' table, kitchen, utensils, etc., where they come in contact with the chemical solution in the form of detergents or disinfectants. The safety level of solutions differs from one to another. Most products must comply with specific safety standards before

entering the market for general use. However, the individual response among food handlers towards the chemical solution might also differ. During the cleaning process, prolonged exposure to direct contact with the chemical solution, such as cleaning products or solvents, can cause skin irritation, occupational contact dermatitis, or respiratory problems.

### **2.1.3 Biological Hazard**

A biological hazard can be defined as any hazard associated with working with animals, people, or infectious plant materials. In the context of occupational safety and health, food handlers can be carriers of an infective organism and become the index source of infection to other co-workers at the food premises. For example, in the Covid-19 pandemic period, one can easily get infected if the standard operating procedures and guidelines for preventing Covid-19 infection are not followed, such as mask-wearing, hand hygiene, and social distancing. Besides that, food handlers may also come in contact with other common infective agents for foodborne pathogens such as *Bacillus cereus*, *Campylobacter jejuni*, *Clostridium botulinum*, *Clostridium perfringens*, *Cronobacter sakazakii*, *Escherichia coli*, *Listeria monocytogenes*, *Salmonella spp.*, *Shigella spp.*, *Staphylococcus aureus*, *Vibrio spp.* and *Yersinia enterocolitica*, viruses (*Hepatitis A* and *Noroviruses*) and parasites (*Cyclospora cayetanensis*, *Toxoplasma gondii* and *Trichinella spiralis* (Bintsis, 2017). Food handlers who are at active infection, or carriers, can transfer these pathogens into the food and compromise their health and food safety if good hand hygiene is not in practice.

### **2.1.4 Mechanical Hazard**

A mechanical hazard can be defined as any hazard associated with the moving parts of a machine or work equipment. For example, a food handler working at the

meat processing branch often uses sharp and dangerous hand tools. During the initial part of the raw materials process, sharp and heavy butcher's knives are routinely used to cut and trim the meat by hand. As the working area where the cutting and trimming process can get wet and slippery, the proper boot can reduce the risk of slipping and falling. One must also be skilled in handling the knives. A food handler might have to deal with a slaughter machine, meat cutting machine, or meat mincer machine at another segment. The machine must be dealt with high safety precautions as improper handling might cause severe physical injuries leading to temporary or permanent disabilities or even death (Tomoda & International Labour Office. Industrial Activities Branch., 1993).

#### **2.1.5 Psychosocial Hazard**

Psychosocial hazards can be defined as stressors that cause stress (short-term effects) and strain (long-term effects). These hazards are related to issues at the workplace such as workload, lack of control, respect, etc. Food handlers are commonly perceived as low-skilled occupations that do not require high-order thinking skills. At food premises, it is not uncommon to see that some workers work at the same level for years as there is little opportunity for career progression. Most of them work in the unorganized sector. The food handlers are also often exploited with low wages that are incomparable to their actual skills, strenuous activity, and restricted leave. The stress they have to endure regarding their duty might toll their mental and physical health (Dudeja & Singh, 2017).

## **2.2 KNOWLEDGE, ATTITUDE, AND PRACTICE (KAP) ON OCCUPATIONAL SAFETY AND HEALTH AMONG FOOD HANDLERS**

As food handlers will be exposed to various types of hazards, all food handlers must be equipped with good KAP to prevent occupational-related injury and

diseases among food handlers working in the food and beverages industry. The food handlers equipped with good knowledge of occupational safety and health would allow them to perform their duty safely. Good knowledge will encourage the workers always to put safety and health as the main priority, creating a safe climate at work. Positive attitudes towards occupational safety and health-related activities can be seen, for example, via active participation among workers in safety and health training organized by the organization and their compliance with safety and health-related policy and regulations at work and vice versa. Excellent practice, action, or behavior towards occupational safety and health at work may reduce the risk of accidents. Exploring KAP of workers toward occupational safety and health can be used to aid in evidence-based intervention, which can improve work situations or the target behavior (Goh & Chua, 2016).

### **2.3 FACTORS ASSOCIATED WITH KNOWLEDGE, ATTITUDE, AND PRACTICE AMONG FOOD HANDLERS**

In the literature review, there were limited studies found under the specific theme of occupational safety and health among food handlers at food premises. The literature commonly ends up with a study that look into the theme of food safety and food hygiene rather than food handler's safety and food handler's health. However, upon revising the training module on food safety and food hygiene of few agencies such as MOH, there were also component of occupational safety and health in the module that been taught to food handlers, but from the point of view of food safety and food hygiene such as hand washing practices (MOH, 2014). From food safety and food hygiene point of view, hand washing should be practiced by food handlers to prevent food contamination. However, from the occupational safety and health point of view, the objective of hand washing practices is to protect the food handlers from getting themselves infected for example, by infectious animals or plants.

Due to the limitation and the common similarities found in the training module of food safety and food hygiene, literature review on factors associated with KAP on

occupational safety and health at food premises will also include such study and presented in the table as shown below. The factors found can be categorized into sociodemographic, socioeconomic, working experience and previous training:

| Variable | Reference   | Study Details                                                                                                                  | Findings                                                                                         | p value |
|-----------------|--------------------|---------------------------------------------------------------------------------------------------------------------------------------|---------------------------------------------------------------------------------------------------------|----------------|
| Age             | (Nee & Sani, 2011) | Assessment of Knowledge, Attitudes and Practices (KAP) Among Food Handlers at Residential Colleges and Canteen Regarding Food Safety. | There was no statistical difference between the knowledge aspects and the age groups.                   | p>0.05         |
| Age             | (Nee & Sani, 2011) | Assessment of Knowledge, Attitudes and Practices (KAP) Among Food Handlers at Residential Colleges and Canteen Regarding Food Safety. | There was no statistical difference between the attitude aspects and the age groups.                    | p>0.05         |
| Age             | (Nee & Sani, 2011) | Assessment of Knowledge, Attitudes and Practices (KAP) Among Food Handlers at Residential Colleges and Canteen Regarding Food Safety. | There was no statistical difference between the practice aspects and the age groups.                    | p>0.05         |
| Gender          | (Nee & Sani, 2011) | Assessment of Knowledge, Attitudes and Practices (KAP) Among Food Handlers at Residential Colleges and Canteen Regarding Food Safety. | There was no significant difference in average points of knowledge with respect to the gender variable. | p>0.05         |
| Gender          | (Nee & Sani, 2011) | Assessment of Knowledge, Attitudes                                                                                                    | There was no significant different                                                                      | p>0.05         |

|                    |                          |                                                                                                                                                                                                             |                                                                                                                                                                                                   |             |
|--------------------|--------------------------|-------------------------------------------------------------------------------------------------------------------------------------------------------------------------------------------------------------|---------------------------------------------------------------------------------------------------------------------------------------------------------------------------------------------------|-------------|
|                    |                          | and Practices (KAP) Among Food Handlers at Residential Colleges and Canteen Regarding Food Safety.                                                                                                          | in average points of attitude with respect to the gender variable.                                                                                                                                |             |
| Gender             | (Nee & Sani, 2011)       | Assessment of Knowledge, Attitudes and Practices (KAP) Among Food Handlers at Residential Colleges and Canteen Regarding Food Safety.                                                                       | There was significant different in average points of practice with respect to the gender variable.                                                                                                | $p < 0.05$  |
| Level of Education | (Alemayehu et al., 2021) | Food Safety Knowledge, Handling Practices and Associated Factors Among Food Handlers Working in Food Establishments in Debre Markos Town, Northwest Ethiopia, 2020: Institution-Based Cross-Sectional Study | Food handlers who did not attain any formal education were 77.0% less likely to have good food safety knowledge as compared to those food handlers who had completed secondary educational level. | $P < 0.001$ |
| Working experience | (Nee & Sani, 2011)       | Assessment of Knowledge, Attitudes and Practices (KAP) Among Food Handlers at Residential Colleges and Canteen Regarding Food Safety.                                                                       | There was a significant difference between the knowledge aspect and the duration of working experiences.                                                                                          | $p < 0.05$  |
| Working experience | (Nee & Sani, 2011)       | Assessment of Knowledge, Attitudes and Practices (KAP) Among Food Handlers at Residential Colleges                                                                                                          | There was no significant difference between the attitude aspect and the duration of working experiences.                                                                                          | $p > 0.05$  |

|                        |                       |                                                                                                                                                               |                                                                                                          |          |
|------------------------|-----------------------|---------------------------------------------------------------------------------------------------------------------------------------------------------------|----------------------------------------------------------------------------------------------------------|----------|
|                        |                       | and Canteen
Regarding Food
Safety.                                                                                                                      |                                                                                                          |          |
| Training
attendance | (Nee & Sani,
2011) | Assessment of
Knowledge, Attitudes
and Practices (KAP)
Among Food
Handlers at
Residential Colleges
and Canteen
Regarding Food
Safety. | There was no
significant difference
between knowledge
and attendance to
training course.     | $p>0.05$ |
| Training
attendance | (Has et al.,
2018) | An Assessment on
Pre- and Post-Food
Hygiene Training on
Food Safety's KAP
Level Among Food
Handlers In Kuala
Terengganu And
Kuala Nerus  | There was a
significant difference
in knowledge scores
pre- and post-food
hygiene training.  | $p<0.05$ |
| Training
attendance | (Nee & Sani,
2011) | Assessment of
Knowledge, Attitudes
and Practices (KAP)
Among Food
Handlers at
Residential Colleges
and Canteen
Regarding Food
Safety. | There was no
significant difference
between practice
and attendance to
training course.      | $p>0.05$ |
| Training
attendance | (Nee & Sani,
2011) | Assessment of
Knowledge, Attitudes
and Practices (KAP)
Among Food
Handlers at
Residential Colleges
and Canteen
Regarding Food
Safety. | There was
significant difference
between attitude
and attendance to
training course.         | $P<0.05$ |
| Training
attendance | (Has et al.,
2018) | An Assessment on
Pre- and Post-Food
Hygiene Training on
Food Safety's KAP
Level Among Food                                                        | There was no
significant difference
in attitudes scores
pre- and post-food
hygiene training. | $p>0.05$ |

|                                    |                                |                                                                                                                                                       |                                                                                                          |        |
|------------------------------------|--------------------------------|-------------------------------------------------------------------------------------------------------------------------------------------------------|----------------------------------------------------------------------------------------------------------|--------|
|                                    |                                | Handlers In Kuala Terengganu And Kuala Nerus                                                                                                          |                                                                                                          |        |
| Training attendance                | (Has et al., 2018)             | An Assessment on Pre- and Post-Food Hygiene Training on Food Safety's KAP Level Among Food Handlers In Kuala Terengganu And Kuala Nerus               | There was a statistically significant difference in practice scores pre- and post-food hygiene training. | p<0.05 |
| Supervisor practices (Active)      | (Mohd Ishanuddin et al., 2019) | An Investigation of Knowledge, Attitude and Practice of Occupational Safety and Health (OSH) on Safety Climate at Workplace in Manufacturing Industry | Knowledge and active practices factors showed positive moderate correlation.                             | p<0.01 |
| Supervisor practices (Proactive)   | (Mohd Ishanuddin et al., 2019) | An Investigation of Knowledge, Attitude and Practice of Occupational Safety and Health (OSH) on Safety Climate at Workplace in Manufacturing Industry | Knowledge and proactive practices factors showed positive moderate correlation.                          | p<0.01 |
| Supervisor practices (Declarative) | (Mohd Ishanuddin et al., 2019) | An Investigation of Knowledge, Attitude and Practice of Occupational Safety and Health (OSH) on Safety Climate at Workplace in Manufacturing Industry | Knowledge and declarative practices factors have a strong positive correlation.                          | p<0.01 |

